#### Sample size and recruitment

The sample size was calculated considering the prediction of a 1.5 point increase in the food knowledge score after the intervention, with a standard deviation of 2.9 [58], a significance level of 5%, and power of 80%. Under these conditions, the minimum sample should be of 60 individuals per group, with control of the participants’ gender. Adding an estimated 40% loss between the pre- and post-intervention moments, the minimum total sample is defined as 168 individuals (84 per group). Each class in private schools has approximately 35 students [57]. Considering an estimate enrollment of 21 participants per class (40% of refusal), we expect to enroll 8 schools in the study, which will be randomly selected to form the study groups: 4 in the intervention group and 4 in the control group.

To recruit the selected school units, we will use email, telephone, and in-person visits to contact each school and explain our research. After the schools agree to participate and sign a consent form, we will select 1st-year high school classes and schedule visits to explain the study to students. Those who verbally agree to participate will be asked to request the written consent of their parents or legal guardians. Finally, the students’ assent will be obtained. Figure 1 shows the flowchart of recruitment and intervention of the study.

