#### Intervention group

Adolescents in the intervention group will be instructed to play the game, and the first contact will occur at the school. Because of its autonomous nature, the intervention will not be included in the school curriculum. To increase the intervention group’s motivation, an environment of challenge and social interaction will be created among the students of each school, based on a competition of time spent to finish the game. These aspects are considered important by adolescents who play games [33, 62, 64]. The students will be able to play *Rango Cards* at school and also at the time and place which are more convenient for them. The period to play will be 3 weeks, and then a post-intervention questionnaire will be applied. This autonomy, which reflects “the will to perform a task,” aims to improve intrinsic motivation [64].

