#### Data analysis

After data collection, the questionnaires will be entered into electronic spreadsheets. To ensure data reliability, data will be double entered. Sociodemographic variables will be analyzed descriptively and expressed as mean, standard deviation, and frequencies. The Pearson’s chi-squared test will be used for sex and age, while the Mann-Whitney U test will be used for family income and maternal level of education. To assess the impact of the intervention, unpaired analyses will be performed using the Student’s t-test for continuous numerical variables (dietary perceptions) and Likert-type scales (food knowledge and self-efficacy). The Mann-Whitney U test will be used for dietary practices and food consumption. The significance level will be set at 5%, and the statistical analyses will be performed using the Statistical Package for the Social Sciences (SPSS), version 21.0.

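### A 40% expected loss is met only by enlarging the sample, while the fixed unpaired t-test leaves the primary comparison open to bias if loss is selective in a way that differs between groups

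*Protocol article*

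**What the plan says.** Under Sample size and recruitment, the article bases the trial on "the prediction of a 1.5 point increase in the food knowledge score after the intervention", with a standard deviation of 2.9, a 5% significance level and 80% power. From this it concludes that "the minimum sample should be of 60 individuals per group". It then allows for attrition, "Adding an estimated 40% loss between the pre- and post-intervention moments", and arrives at 84 per group, 168 in total. Eight schools are to be allocated, "4 in the intervention group and 4 in the control group".

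Food knowledge and self-efficacy are named as the primary outcomes at the end of Game components. Under Measures, both groups complete the same questions before and after the intervention, sociodemographic items aside. Under Intervention group, the playing period is 3 weeks and one post-intervention questionnaire follows.

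Under Data analysis, the impact of the intervention on both primary outcomes is to be tested as follows: "unpaired analyses will be performed using the Student’s t-test".

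The groups are handled differently in between. In the intervention schools, "an environment of challenge and social interaction will be created among the students of each school", built around a competition on time to finish the game. Under Control group, students are not told to play and receive no material.

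**The concern.** The article states a loss figure and a primary test, and the two fit poorly. A two-sample t-test, on post-test scores or on change scores, needs a post-test value for each student it includes. Students who leave after the pre-test contribute nothing, although their answers to the same questions are already in hand. On the plan's own expectation, that is two students in five.

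The only stated response to the loss is a larger enrolment. That addresses precision. It does nothing about whether the students who remain in one group are still comparable with those who remain in the other. Because only the intervention group has a game and a competition, the reasons for staying or leaving may differ between groups. If they do, the completers' difference mixes the effect of the game with the effect of who stayed, and the significance test no longer has its nominal error rate.

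**Working it through.** **Inputs from the article (Sample size and recruitment):** difference 1.5 points, SD 2.9, two-sided 5% (the sidedness is not stated, but one-sided gives 47 per group and does not fit), power 80%, loss 40%, 84 enrolled per group.

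**Reproducing the plan's figure.** n per group = 2 × [2.9 × (1.960 + 0.842) / 1.5]² = 58.7, so 59 by the normal approximation. The exact t-test calculation gives 59.7, so 60. The stated 60 reproduces. The 84 is 60 × 1.40. After 40% loss, 84 × 0.60 = 50.4 students per group remain.

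**Bias formula.** Let *p* be the share lost in a group and *D* the mean score of retained students minus that of lost students. The completers' mean exceeds the full-group mean by *p* × *D*. The bias in the group difference is therefore

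bias = *p*(I) × *D*(I) − *p*(C) × *D*(C), with I for intervention and C for control.

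It is zero when both groups share the same *p* and the same *D*, however large *p* is.

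**Standard error with no clustering.** With 50.4 per group: 2.9 × √(2/50.4) = 0.578. With 45% and 35% loss, 46.2 and 54.6 remain: 2.9 × √(1/46.2 + 1/54.6) = 0.580.

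**Scenarios.** The article gives no loss by group and no score gap, so every rate split and gap below is an assumption. 0.25 SD = 0.725 points and 0.5 SD = 1.45 points. The rejection rate is that of the two-sided 5% t-test when the game has no effect (noncentral t distribution).

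| Loss, I / C | Gap, I / C | Bias (points) | Share of 1.5 | Rejection rate |
|---|---|---|---|---|
| 40% / 40% | equal, any size | 0 | 0% | 5% |
| 45% / 35% | 0.5 SD / 0.5 SD | (0.45 − 0.35) × 1.45 = 0.145 | 10% | 5.7% |
| 40% / 40% | 0.25 SD / none | 0.40 × 0.725 = 0.29 | 19% | 7.9% |
| 40% / 40% | 0.5 SD / none | 0.40 × 1.45 = 0.58 | 39% | 16.9% |

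Swapping the two groups changes the sign of the bias and leaves its size and the rejection rate unchanged.

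**The case against.** The strongest objection is that this is a missing-data policy that a condensed article may leave to a fuller document. Nothing under Data analysis restricts the t-test to students with a post-test, a t-test can be run on imputed data, and inflating a sample for loss is routine. This stands in part. The restriction to completers is inferred from how the test works and from the way the sample size allows for loss, and an analysis plan that is not shown could add imputation. For that reason the point does not rest on the absence of a missing-data section, or of a table comparing completers with lost students. It rests on the test that the article does fix, and on a better use of data that it does plan to collect.

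A reader might also infer that 40% loss alone biases the test, or that it does so whenever lost students score differently from those kept. That is the condition for a biased group mean. For the group difference, equal rates and equal gaps cancel.

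A reader might further infer that the loss will flatter the game, because uninterested students would leave mainly from the intervention group. The article does not support that direction. The competition is meant to raise motivation and could as easily keep students in. At least two researchers supervise the questionnaires, and each school is to be visited at least three times, so loss through absence on a visit day, similar in both groups, is also plausible.

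Finally, a model of pre and post scores is not a full cure. With a single post-test, it removes only the bias from loss that observed data explain. That also stands, and it is the reason for the sensitivity analysis in the fix.

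**Conclusion.** The concern holds in a conditional form. What is certain from the text is that the plan expects 40% loss, responds only by enlarging the sample, and fixes a test that, as written, uses only students with a post-test and makes no stated use of baseline scores to deal with the loss. What is not certain is whether bias will arise, how large it would be and which way it would point.

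Under the assumed scenarios the bias runs from 0 to 0.58 points, at most 39% of the target difference, with error rates from 5% to about 17%. The upper figure requires a half-SD gap in one group and none in the other, and should not be quoted as an expected result. All figures assume an SD of 2.9, 84 enrolled per group and independent students. The allocation of whole schools is left aside.

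The change is worth making because it is cheap and uses data already planned. Confidence is high on the mismatch and low on the size of its consequence.

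**What to change.** Under Data analysis, replace the unpaired t-test for food knowledge and self-efficacy with a linear mixed model of the pre and post scores of all enrolled students. Fixed effects: group, time, group-by-time (the intervention effect) and sex. Random effects: school and student. Use a small-sample degrees-of-freedom correction, since there are only 8 schools. An acceptable alternative is multiple imputation of missing post-test scores from baseline score, sex, school and group.

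State in the same section that either approach removes only the bias from loss explained by observed data. Add one sensitivity analysis that shifts the imputed post-test scores by 0.25 and 0.5 SD, in either group in turn and in either direction, and reports how the estimated effect and its interval change. With 40% imputed in a group, these shifts move that group's mean by 0.29 and 0.58 points, so the analysis covers the range worked out here.

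The cost is revised wording and modest programming, and the reported interval may be wider. No new data collection or extra visits are needed.

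### As the text reads, schools are put into arms before classes are chosen and students consent, with no stated concealment, so with 40% refusal expected the arms may enrol different kinds of students

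*Protocol article*

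**What the plan says.** The Sample size and recruitment section sets out the steps in this order.

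1. Allocation: "we expect to enroll 8 schools in the study, which will be randomly selected to form the study groups: 4 in the intervention group", with the other four schools as controls.
2. School contact: "To recruit the selected school units, we will use email, telephone, and in-person visits to contact each school and explain our research".
3. Class choice and approach to students: "After the schools agree to participate and sign a consent form, we will select 1st-year high school classes and schedule visits to explain the study". No rule is given for choosing the class.
4. Parental consent: "Those who verbally agree to participate will be asked to request the written consent of their parents or legal guardians".
5. Student assent: "Finally, the students’ assent will be obtained".

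The same section expects about 35 students per class, of whom 21 enrol and 40% refuse. The Study design section places written consent before the study begins, but does not say that it precedes allocation. The Intervention group section describes play over three weeks with a competition among the students of each school. The Control group section says those students are not told to play and are given no healthy-diet material. The Data analysis section plans an unpaired Student's t-test for food knowledge and self-efficacy. It does not say whether the post-intervention score or the change is compared, and it states no baseline adjustment.

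**The concern.** Drawing eight schools at random makes the schools comparable in expectation. It does not do the same for the students if they are identified and agree to join after their school's arm is known. Three choices in this plan could then depend on the arm: which class the team picks, how the team presents the study, and whether the student and parents say yes.

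The conditions for this are present. Two in five of those approached are expected to refuse, so there is ample room for self-selection. The arms differ sharply in what they offer a teenager. The primary outcomes, food knowledge and self-efficacy in healthy practices, are plausibly related to interest in the subject. An unpaired comparison of post-intervention scores would carry any recruitment difference straight into the estimated effect.

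A second route concerns the schools themselves. If a school declines after the draw, the 4+4 allocation is disturbed, and the text gives no rule for replacing it.

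**Working it through.** **Order of the steps.** Two phrases carry the reading. The schools are those "8 schools in the study, which will be randomly selected to form the study groups", and the next paragraph opens with "To recruit the selected school units, we will use email, telephone, and in-person visits". Read in sequence, the schools contacted are the ones already drawn, and class choice, parental consent and assent all come later. No sentence gives an explicit time for the allocation, and none says who knows it at consent.

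**The plan's own figures.**
- Sample per group: a difference of 1.5, SD 2.9, two-sided 5% and 80% power give 59.65 from the t-based calculation, rounded up to 60. This matches the plan.
- Enrolment: 35 × (1 − 0.40) = 21 per class; 21 × 8 = 168 in total; 21 × 4 = 84 per group. This matches the plan.

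**Size of a possible shift (illustration).**

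Inputs from the protocol: 60% of students join, SD 2.9, target effect 1.5 points, 60 analysed per group.

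Assumptions not in the protocol: willingness to join is normally distributed and the most willing 60% join; willingness has correlation r with the knowledge score in one arm and zero in the other.

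- The cut-off for the top 60% is z = −0.2533. The mean standardised willingness of those who join is φ(−0.2533)/0.6 = 0.644.
- Shift in that arm's mean score = r × 0.644 × 2.9 = r × 1.867.
- Standard error of the difference with 60 per group, ignoring clustering: 2.9 × √(2/60) = 0.529.

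| r in one arm | Shift (points) | Share of 1.5 | Rejection rate of nominal 5% test with no true effect |
|---|---|---|---|
| 0.1 | 0.19 | 12% | about 6% |
| 0.2 | 0.37 | 25% | about 11% |
| 0.3 | 0.56 | 37% | about 18% |

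**If both arms select.** With the same 60% joining in each arm, the shift becomes (r₁ − r₀) × 1.867. At r₁ = 0.3 and r₀ = 0.2 it is 0.1 × 1.867 = 0.19. At equal correlations it is zero.

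**If change scores are compared.** A baseline difference that stays constant over the three weeks cancels. A difference in motivation to learn does not, because it affects the gain itself.

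**The case against.** The strongest reply is that the order is inferred. The allocation sentence closes a paragraph of sample-size arithmetic, which is not a timeline. It speaks of schools expected to be enrolled, so it can be read as enrol first, then allocate. The selected schools in the next paragraph could be schools sampled from the private-school population. The text refers to Figure 1 for recruitment, and that figure may settle the matter. This stands as a limit on certainty. The sequence of sentences still favours the reading given here, and nothing in the text rules it out.

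A reader might go further and infer that researchers do choose classes knowing the arm, and that students do decide knowing whether they will get a game. The protocol does not support that. It describes one recruitment procedure for all schools, and its sections on the two groups describe what happens in the study, not what is said at consent. Knowledge of the arm is a possibility that the text leaves open.

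The illustration can also be called one-sided. That is fair: 40% refusal is planned for every class, general interest in a nutrition study could act alike in both arms, and the correlations come from no document. The baseline questionnaire in both groups would make a difference in baseline knowledge visible.

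Finally, concealment details and consent scripts are commonly left to a full protocol. That holds for the details. The point here is the order of steps that the article itself sets out.

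**Conclusion.** The point holds as a risk that the plan as written permits; it is not a demonstrated bias. The text places the formation of the 4+4 groups ahead of school contact, class choice and consent, and says nothing about concealing the arm at those steps. With 40% refusal and unequal appeal of the two arms, the arms may enrol different kinds of students, and a school declining after the draw would disturb the allocation.

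The plausible size is 0.19 to 0.56 points, or 12% to 37% of the 1.5-point target. This rests on correlations of 0.1 to 0.3 in one arm and none in the other, which are assumptions. The shift would be smaller if selection is similar in both arms or if change scores are analysed. The sequence should be changed, or stated explicitly if consent before allocation was intended, because self-selection after allocation cannot be undone once students have enrolled.

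**What to change.** State and follow this order:

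1. Sign up all eight schools.
2. Choose the class in each school by a random draw or a rule fixed in advance.
3. Obtain parental consent and student assent with one neutral script used in every school.
4. Complete the baseline questionnaire.
5. Only then draw, or reveal, the allocation of four schools to each group.

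Report the numbers approached and refusing by arm. If Figure 1 already shows this order, bring the text into line with it.

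The schools, students, questionnaires and sample size stay the same. The cost is in scheduling: all eight schools must finish consent and baseline before any school starts the game. This may delay the start or separate the baseline visit from the visit that introduces the game. The protocol foresees at least three visits per school but does not say what each one covers, so whether an extra visit is needed has to be checked.

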**Fig. 1 Fig1:**
[figure not shown]
Study Procedure Flow Diagram

### Intervention

#### Rango cards development process

A team of dietitians, Fira Soft® game developers, and adolescents was involved in the development of a digital game. As a preliminary activity, the hired company informally collected opinions about two game mechanics from adolescents and young adults (13–24 years) who play games frequently. We chose the mechanics and format of Hearthstone® (Blizzard Entertainment), named the best multiplayer game by Google Play in 2017 [59]. After setting the basic structure of the game, the concepts of art and user interface were created, as well as the game design document. A convenience sample of adolescent players was selected to be part of the production team and participate in all assessments of viability, usability, and attractiveness of the mobile application. They were all interested in the topic and their age group (14–16 years) was compatible with the target audience of the game.

The developed tool can be classified as a serious game. It is free, compatible with Android and iOS devices, and available from Google Play and App Store since April 2017. The name *Rango Cards* was chosen because it links the word “rango” (an informal word in Brazilian Portuguese to refer to food) to the word “cards” (the type of game). The mechanics of card games explores the strategic potential of each player. Social cognitive theory was used to develop the game [32, 60].

The visual style of the game was based on the preferences expressed by the adolescents, favoring a cheerful, simple, and friendly atmosphere. The cards were differentiated by color, in line with the logic of other games and also the traffic lights. Thus, green cards represent healthy foods and/or meals that should be consumed regularly; yellow cards represent foods that should be consumed moderately; and red cards represent foods that should be avoided, as recommended by the *Dietary Guidelines for the Brazilian Population* [19]. There are also cards of characters and healthy practices, such as cooking and having meals at clean environments and in the company of other people, thus showing that the concept of a healthy diet is not associated only with food intake.

The game uses a real-time system of sodium, sugar, and fat content meters, which change when the player uses cards of processed or ultra-processed foods. In the game, these are called industrialized and mega-industrialized foods, respectively. The meters influence the playability and the fate of the player in a match. At first, the effect seems mild, but as the player uses more unhealthy food cards the damages become more evident, impacting health and energy levels and the remaining time to play.

The virtual environment where the narrative of *Rango Cards* takes place is a school with typical spaces (schoolyard, library, auditorium) and characters, except for the third phase, when the player visits a restaurant. The scenario for the matches is a dining table. Characters are ethnically diverse and wear simple clothes to facilitate the player’s identification with the illustrations. Features of Japanese animation (anime) and American comic books were used. To engage players, contextualize the game, and simplify the transposition of concepts, the phases were interspersed with dialogue scenes, which tell a linear narrative and involve all the game characters. This contributes to increase the immersion in the game experience and the intrinsic motivation to play. As recommended by Hingle et al. [61], dialogues are short and objective.

The difficulty level of the game oscillates between easy and hard. This required a two-step calibration, as follows: first, the cards were balanced and then the decks were compiled, one by one, in the order they appear in the game. Regarding card attributes, the greater the effect of a card in the game, the higher its cost to the player, i.e., the higher the amount of energy required to make a move. The idea is to show that choices are significant and may result in winning or losing. In the first phase, the deck consists of 23 cards; from the fifth phase on, the player has access to the full 44-card deck. The logic is to gradually introduce new concepts and improve the player’s skills.

#### Game components

To initiate the game, the player needs to complete a brief profile and choose a female or male avatar. Then, a school character invites the player to participate in a new health and diet training by playing a card game. Each phase includes computer-controlled opponents, i.e., this is not a player vs. player game. The game environment components are the following: a) energy markers; b) card deck; c) avatar, opponent, and foods, which are grouped according to the classification described in the *Dietary Guidelines for the Brazilian Population* [19]. Each character has a health score accompanied by sodium, sugar, and fat content meters. Figure 2 shows the game components of *Rango Cards*.

